## Practice and Patient Selection: Inclusion and Exclusion Criteria

### Practice eligibility

Practices are eligible to take part if they:

• Have a practice nurse, involved in general patient care (to be confirmed at the initial practice visit).

• Did not participate in the pilot phase of the study.

#### For practices in the Republic of Ireland

• Are not participating in Heartwatch (a national pilot programme in the Republic of Ireland on the provision of secondary care in general practice, currently ongoing).

• Have a minimum General Medical Scheme (GMS) list size of 700 patients. Based on an Irish prevalence rate of 3.16% for CVD [7], this will ensure at least 22 eligible GMS patients per practice, a figure which will be supplemented by non-GMS patients.

#### For practices in the North of Ireland

• Have a minimum NHS list size of 1800 patients. Based on a UK prevalence rate of 2.6% for CVD [4], this will ensure at least 40 eligible patients per practice.

### Patient eligibility

#### Inclusion criteria

Patients with existing cardiovascular disease (defined as: documented MI, CABG or angioplasty, or a diagnosis of angina – confirmed by exercise stress test, isotope test or coronary angiogram) are eligible for inclusion.

#### Exclusion criteria

Patients with significant mental or physical illness (based on the recorded judgement of practice staff), which is likely to impair capacity to change lifestyle behaviour or assimilate new information, are not included.

## Sample Size Calculation

The study aims to achieve a final sample of 635 patients from at least 42 practices (see Figure 1).

**Figure 1 F1:**
[figure not shown]
Flow of Practices and Patients Throughout Trial.

Sample size calculations are based on the following:

• Power of 80% and alpha of 5%.

• Only patients agreeing to participate in the study and completing baseline data collection will be entered into the study. There will, therefore, be 100% uptake at the start of the study. Reasons for non-participation will be documented and recorded, and participation rates will provide a measure of the acceptability of this type of intervention to patients.

• A final completion rate of 70% is anticipated based on similar studies in the West of Ireland 7 (completion rate = 68.7%) and Dublin [28] (completion rate = 93%).

• Practice attrition of 12.5% has been allowed for (though practice attrition in another similar study was only 4% [28]).

• Improvements in the control group as a result of participation in a research study have been anticipated [25].

• Design effects are calculated using intracluster correlation coefficients from data from similar populations in Galway and Scotland ([name], personal communication).

A total sample size of 907 patients recruited from 46 practices gives a varying but minimum power of 80% to detect significant changes in proportions with poor blood pressure and cholesterol control, physical and mental well being (SF-12) and hospital readmissions at two years. (Detailed power calculations are given below). This allows for a final patient follow-up and retention rate of 70% and a practice attrition rate of 10%. The number of practices is rounded up from 46 to 48, to allow equal numbers of practices to be recruited in each of the three study centres. Sixteen practices will therefore be recruited in each of the three centres, eight intervention practices and eight control practices. Twenty patients are recruited in each practice. Final data analysis will incorporate modelling techniques that are more statistically efficient and will ensure greater power to detect significant changes in study outcomes.

## Power Calculations – Further Detail

### Blood pressure

44% of Irish patients with established heart disease have a systolic blood pressure above recommended guidelines (SBP >140 mmHg) ([name], personal communication). Previous research indicates that an improvement of 20% can be anticipated in the control group [10]. Taking this into consideration, a sample size of 408 gives 80% power to detect a 50% reduction in the proportion of patients with a SBP above 140 mmHg (i.e. giving a proportion of 22%) in the intervention group with a corresponding 20% improvement in the control group. Other studies have indicated that it is possible to achieve similar targets in general practice populations with established coronary heart disease [15]. To take account of cluster randomisation, based on recruiting 15 patients per cluster, a design effect size of 1.15 and an intracluster correlation coefficient of 0.011 [4,10] suggests a sample size of 470 patients from 31 practices. Allowing for a final response rate of 70% and a practice attrition rate of 10% requires recruitment of 670 patients from 34 practices.

### Cholesterol

36% of Irish patients have a baseline cholesterol level above the upper recommended limit, i.e. greater than 5 mmol/l ([name], personal communication). To demonstrate an improvement of 50% in the intervention group and 20% in the control group requires a sample size of 500 patients. To ensure a final sample of 15 patients per practice, this is inflated by a design effect size of 1.27 (ICC = 0.019; [name], personal communication) to give a sample of 635 patients from 42 practices. This is increased to 907 patients from 46 practices to allow for final follow up and response rate of 70% and practice attrition of 10%.

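### The 907-patient target covers patient loss only; if practice attrition is a separate loss, as the text lists it, the expected final sample is about 588–605 rather than 635, and cholesterol power is slightly below 80%

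*Protocol article*

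**What the plan says.** All references are to the protocol article.

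- **Sample Size Calculation, aim:** "The study aims to achieve a final sample of 635 patients from at least 42 practices".
- **Same section, list of assumptions:** "Power of 80% and alpha of 5" per cent; an anticipated final completion rate of 70%; and "Practice attrition of 12.5% has been allowed for".
- **Same section, closing paragraph:** 907 patients from 46 practices are said to give at least 80% power for every primary outcome. On the losses: "This allows for a final patient follow-up and retention rate of 70% and a practice attrition rate of 10" per cent. The practices are then rounded up to 48, with 20 patients in each.
- **Cholesterol, inputs:** "36% of Irish patients have a baseline cholesterol level above the upper recommended limit"; "To demonstrate an improvement of 50% in the intervention group and 20% in the control group requires a sample size of 500 patients"; "this is inflated by a design effect size of 1.27 (ICC = 0.019"), for a final 15 patients per practice. This gives 635 patients from 42 practices.
- **Cholesterol, inflation:** the 635 is "increased to 907 patients from 46 practices to allow for final follow up and response rate of 70% and practice attrition of 10" per cent.

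The Blood pressure, SF-12 and Hospital re-admissions sections name the same pair of allowances.

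**The concern.** The text names two losses and says the recruitment target covers both. The step from 635 to 907 is fully explained by one of them. Practices that withdraw take their patients with them, so if practice attrition comes on top of patient loss, the patient count falls short of the final sample it was built to deliver. Two practice attrition rates, 12.5% and 10%, also stand in the same section without explanation.

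Cholesterol has the largest requirement of the four primary outcomes and so sets the size of the trial. At stake are the stated final sample and the stated power floor for that outcome.

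**Working it through.** **1. Reproduce the plan's 500.** Control: 36% × 0.8 = 28.8%, taken as 29%. Intervention: 36% × 0.5 = 18%. Difference d = 0.11, mean proportion 0.235, two-sided 5% (sidedness is not stated, but two-sided reproduces the figure), 80% power.

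- Uncorrected, per arm: n = [1.960·√(2 × 0.235 × 0.765) + 0.842·√(0.29 × 0.71 + 0.18 × 0.82)]² / 0.11² = 232.05.
- Continuity-corrected: n′ = (n/4)·[1 + √(1 + 4/(n·d))]² = 249.9, so 250 per arm and **500** in total, as stated.
- The same method with 35% vs 22% gives the 408 stated for blood pressure. Uncorrected, the cholesterol total would be 466 (29%) or 482 (28.8%).

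**2. Reproduce 635 and 907.** Design effect 1 + (15 − 1) × 0.019 = 1.266, stated as 1.27; 500 × 1.27 = **635**; 635/15 = 42.3 practices. Then 635/0.70 = 907.1, so **907** comes from patient loss alone. The 46 practices are 42 × 1.10 = 46.2, so the 10% enters the practice count but not the patient count.

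**3. The other outcomes follow the same pattern.** Blood pressure: 470/0.70 = 671 (stated 670). SF-12: 120/0.70 = 171 (stated 170). Readmissions: 406/0.70 = 580 (stated 580).

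**4. Expected final sample if the losses are separate.**

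| Recruited | Practice attrition | Final patients |
|---|---|---|
| 907 | 10% | 907 × 0.70 × 0.90 = 571 |
| 907 | 12.5% | 907 × 0.70 × 0.875 = 556 |
| 960 (48 × 20) | 10% | 960 × 0.70 × 0.90 = 605 |
| 960 (48 × 20) | 12.5% | 960 × 0.70 × 0.875 = 588 |

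In the last row 48 × 0.875 = 42 practices remain with 20 × 0.70 = 14 patients each, not 15. For 635 to remain under both losses, recruitment would be 635/(0.70 × 0.90) = 1,008 or 635/(0.70 × 0.875) = 1,037.

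**5. Cholesterol power at those yields.** With 14 per practice the design effect is 1 + 13 × 0.019 = 1.247. Effective N is 588/1.247 = 472, or 605/1.247 = 485, against 500.

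| Final N | 29% vs 18%, corrected (the plan's method) | 29% vs 18%, uncorrected | 28.8% vs 18%, uncorrected |
|---|---|---|---|
| 588 | 77.5% | 80.6% | 79.3% |
| 605 | 78.7% | 81.7% | 80.4% |

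As a check, 635 at design effect 1.27 returns 80.0% in the first column.

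**6. Other primary outcomes at 588.** Blood pressure (ICC 0.011): about 90% corrected, 91% uncorrected. Readmissions (ICC 0.006): about 91% and 92%. SF-12: close to 100%.

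**7. The other reading.** If 70% is overall completion, lost practices included, 960 × 0.70 = 672 complete. Spread over 42 practices that is 16 each: design effect 1 + 15 × 0.019 = 1.285, effective N 523, and power about 82% by the plan's method.

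**The case against.** The strongest reply is that 70% is the share of all recruited patients who end with usable data, whatever the reason for loss. The figures then fit: 907 × 0.70 = 635, and 635/42 = 15.1 per remaining practice, which is the cluster size used. The practice allowance then protects only the number of practices, consistent with an aim of at least 42. This reading is open, and under it the shortfall disappears. It is not what the text says, however. The outcome calculations list practice attrition beside the 70% as a further allowance in the step to the recruitment figures, and the SF-12 section calls the 70% a patient retention rate.

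Other replies stand in part:

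- **The two attrition rates may be reconcilable.** Going from 48 to 42 practices is exactly 12.5%, while 10% lies behind the 46. This is plausible, but the article does not say so.
- **The result depends on the formula.** Without continuity correction, power is about 79–82%, so the miss is marginal or absent. But that formula does not give the plan's 500. The gap between 588–605 and 635 does not depend on the formula.
- **Actual attrition may be lower.** At the 4% cited from a similar study, 960 × 0.96 × 0.70 = 645, which exceeds 635. The plan chose to size for more than 4%.
- **Modelling may add power.** The article expects this but gives no figure.
- **Rounding of practices** (42/0.90 = 46.7 rather than 46.2) is moot, because 48 are recruited.

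A reader might infer that the 907 target leads to 588 patients, or that the trial is simply underpowered for cholesterol. Neither is supported. The 588 belongs to the 960-patient design at 12.5% attrition, and the power shortfall is conditional on separate losses and on the corrected formula.

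**Conclusion.** The point holds in a limited form. It is certain that 907 equals 635/0.70, so the patient target contains nothing for practice attrition although the text says it does, and that the other three calculations share the omission. It is also certain that 10% and 12.5% appear in one section unreconciled.

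The consequence is conditional. If the losses are separate, as the text lists them, the planned 960 patients yield about 588–605, which is 30 to 47 (5–7%) short of 635. Cholesterol power is then about 77.5–78.7% by the plan's own method, 1.3 to 2.5 percentage points under the stated floor. This assumes ICC 0.019, equal practice sizes and no gain from modelling. Only cholesterol is affected. The fault is a misstated sample size and power, and does not threaten the design.

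**What to change.** In the Sample Size Calculation section and the four outcome calculations:

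1. Use one practice attrition figure, or explain that 10% applies to 46 practices and 12.5% to 48.
2. State whether the 70% already includes patients in practices that withdraw.
3. **If it does not,** restate the expected final sample as about 588–605 patients (14 per practice, design effect 1.247). Give cholesterol power as about 77–79% before any gain from modelling, in place of the claim of at least 80% for every outcome.
4. **If it does,** say so, and drop the claim that practice attrition is a further allowance in the patient count; it then protects only the number of practices.

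The cost is a few restated figures and, under item 3, a slightly less favourable power statement. Recruitment, conduct and analysis do not change.

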### SF-12

A 5 point improvement in the SF-36 has been found to be clinically significant [29]. Based on a mean at baseline of 53.98 (SD 8.39) [7], a sample size of 120 patients is sufficient to detect a clinically significant improvement of 5 points in the SF-12 measure of physical and mental health status in the intervention group. The intracluster correlation coefficient from previous data [7] is <0.0001, indicating that there is no clustering effect for this variable and that the design effect size is 0. Allowing for a patient retention rate of 70% and a 10% practice attrition rate, 170 patients from 10 practices are needed.

### Hospital re-admissions

Northern data ([name], personal communication) indicates that 43% of control patients had hospital admissions in two years. To reduce this by 50% in the intervention group and 20% in the control group needs a sample size of 356 patients. To ensure a final sample of 15 patients per practice, this is inflated by a design effect size of 1.08 (ICC = 0.006) to give a sample of 406 patients from 27 practices, increased to 580 patients from 30 practices to allow for final follow up and response rate of 70% and practice attrition of 10%.

The study acknowledges that smoking is a significant risk factor for cardiovascular disease. For pragmatic reasons smoking has not been used to power the study, as levels of smoking have become low among this population and its measurement would require a sample size too large for the resources available.

## Intervention

### Level 1: Tailored practice care plans

#### (1) Training for practice staff

Training will be delivered independently in each of the three regional study centres. All trainers will adhere to a single training protocol to ensure standardised delivery of the training across centres. Training delivery will be planned and rehearsed jointly by all trainers using role-play and peer review techniques. In addition, the project manager will act as an observer during the first two training sessions in each centre and will provide feedback to trainers with a view to further standardizing the training. The Irish College of General Practitioners (in the Republic of Ireland) and the Northern Ireland Medical and Dental Training Agency (in Northern Ireland) have approved the proposed training sessions for their educational contribution to practitioners' personal development plans.

##### First training session: Medication training

GPs and practice nurses are invited to attend a ninety-minute training session on medication guidelines, delivered by the study GP in each region:

• Belfast: [name], Department of General Practice, Queen's University Belfast.

• Dublin: [name], Department of Public Health and Primary Care, Trinity College Dublin.

• Galway: [name], Department of General Practice, NUI Galway.

This is an interactive session in which practice staff are invited to review and discuss the most recent medication prescribing guidelines for secondary prevention. The session uses case-based scenarios to enable the practitioners to reflect on their own practice. Practitioners are offered a summary sheet of prescribing guidelines and a summary 'prompt' showing commonly used drugs and dosages within the various medication categories. If practices wish their practice nurse to make prescribing decisions the research nurse will help to prepare appropriate specific protocols.

The objectives of this session are:

• To increase confidence and competence regarding prescribing and the secondary prevention of heart disease.

• To discuss the role of the SIGN guidelines and apply to real clinical situations.

• To explore practitioner attitudes to secondary prevention and to discuss points raised specifically by each practice.

• To address issues of patient adherence to medication.

##### Second training session: Behaviour change training

GPs and practice nurses are invited to attend a ninety-minute training session on facilitating patients with behaviour change, delivered by the research nurse in each region. This is an interactive session in which practice staff are invited to reflect on their views around lifestyle change and practice new techniques (through role play) to improve their ability to facilitate patients with behaviour change. Strategies to increase patient motivation are discussed, following guidelines from brief motivational interviewing literature [30,31]. Additional techniques, based on principles of behaviour modification and social learning theory [32], include: setting small achievable goals, action planning, using prompts, self-monitoring, offering rewards, habit reinforcement, and relapse prevention.

The objectives of this session are:

• To enable practitioners to develop skills based on leading behaviour change theories, which may help them with behaviour change consultations.

• To introduce the SPHERE patient-held booklet and the patient care plan (see 'Level 2' below).

#### (2) Responding to individual practice needs

Additional practice needs in relation to the delivery of preventive care for patients with established cardiovascular disease, as well as the day-to day running of the study, are recorded on a tailored practice care plan and followed up by the SPHERE research nurse.

#### (3) Ongoing support from the SPHERE research nurse

The SPHERE research nurse maintains regular contact with the practices, and is easily contactable by phone if practice staff have any queries about SPHERE.

#### (4) SPHERE newsletter

Intervention practices receive a study newsletter which is published every four months. The newsletter contains the latest news and updates relating to the study.

### Level 2: Tailored patient care plans

#### (1) Initial target setting consultations

The first patient intervention consultation with the GP/practice nurse takes place as soon as possible after baseline data collection, once training of practice staff has been completed. BP and BMI are measured, diet, smoking and exercise habits reviewed and the result of the baseline cholesterol assay discussed. The patient and practitioner together identify areas of management which could be improved and the patient is invited to prioritise one particular aspect of their lifestyle for change. Possible ways of achieving targets reflecting optimal management (BP <140/90 mmHg, cholesterol <5 mmol/l, BMI <25, non-smoking, taking exercise for 30 minutes 5 days per week, eating fruit/vegetables daily and avoiding saturated fat intake, avoidance of stress) are identified. Plans for action are recorded on a personal care plan tailored for each patient and retained in the practice. The GP may also see the patient at this visit or at a further appointment within 2 weeks to determine if any change in medication is appropriate. A further follow up telephone call is made by the practice nurse to give support and address any questions 2 weeks later.

#### (2) The patient-held booklet

This booklet contains information on all the key risk factors for CHD. It is used by the practitioners in all initial target setting discussions with the patient and is given to the patient to be kept by them. The booklet can be referred to at subsequent consultations with the GP or practice nurse for consolidation of information relevant to secondary prevention and cardiovascular risk. There are 6 sections in the book:

a) Medications

b) Smoking

c) Exercise

d) Healthy eating

e) Stress

f) Community support

By providing a summary of lifestyle advice for secondary prevention of CHD, the booklet serves not only as an information resource for patients but also as a reference guide to help practitioners in their lifestyle-related consultations with patients.

#### (3) Regular consultations with patients for two years

Patients are invited to attend for an appointment with the GP/nurse every 4 months. At each visit a review of factors relating to targets and goals for optimal secondary prevention are made as appropriate. Goals relating to diet, smoking and exercise habits are routinely reviewed. Cholesterol is checked if it has been found to be raised at baseline, but if normal at baseline cholesterol is checked annually. Relevant measurements taken at each review visit are recorded and held in the practice and reviewed with the patient at subsequent review visits. Care which would be given according to current clinical guidelines will also be provided, as required.

## Control Practices

Data are collected for patients in intervention and control practices in identical ways. In control practices, data are collected at baseline, one and two years post baseline. Otherwise, patients in control practices continue to receive health care as usual and the nature of this in each participating practice will be clearly described.

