The SPHERE Study aims to take these recommendations on board in developing an intervention to improve secondary prevention of CHD in general practice in Ireland. The SPHERE study involves the implementation of a structured systematic programme of care for patients with CHD attending general practice. The SPHERE intervention is multi-faceted and has been developed to respond to the barriers and solutions to optimal secondary prevention identified in preliminary qualitative research with practitioners and patients. The delivery of the intervention is tailored as much as possible to the needs of practices and patients. The process of the intervention will be documented and described in sufficient detail to allow replication of the intervention and to enable identification of effective intervention components. The intervention will be implemented over a 24 month period, with data collection at baseline, 12 months and 24 months. Data collection at these time points will enable identification of any initial and/or sustained changes effected by the intervention. An economic evaluation of the intervention will be carried out. The implementation of the intervention will be monitored throughout the duration of the trial and documented.

In summary, SPHERE will add to what is already known in respect of secondary prevention in primary care, i.e.

• that structured programmes, with continued support and follow-up of patients, help improve recording of process measures of preventive care, patients' functional status, quality of life and lifestyle change [9-11,15,17,25].

• prompts to patients improve their attendance but there is no associated change in measures of risk [13,15].

• structured recall programmes which do not take account of individual practice needs improve recording but not prescribing [15]; provision of training, tailored to practice needs of access to evidence of effectiveness of secondary prevention is associated with improved prescribing [16]

• patient centred consultations impact positively on health outcomes [26] but must be accompanied by attention to disease management guidelines to achieve clinical objectives [27].

SPHERE will:

• record organisational detail of care, in both intervention and control practices

• provide information and training tailored to practices' needs for delivery of secondary prevention

• support patient centred consultations and practitioners' adherence to disease management guidelines.

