### Patient identification (20 patients in each practice)

Participating practices compile a list of all eligible patients (see 'patient eligibility' section below for detail) from their practice and allocate a number to each patient from 1 to Y (where Y is the total number of patients on the list). Research nurses assist the practices in using a list of random numbers to select patients for participation (see additional file 1: Appendix A). A confidentiality agreement will be signed between research nurses and practice staff, to ensure that normal ethical procedures governing each practice are adhered to. Selected patients are posted an invitation letter, information sheet and reply slip (see additional file 2: Appendix B) as well as a questionnaire (see additional file 3: Appendix C). Patients who do not respond within ten days are contacted by a member of the practice staff to ascertain interest in participation. If selected patients do not confirm that they fulfil the eligibility criteria or decline to participate, the next patient on the list is selected until the quota of 20 is reached. The age, gender and diagnostic inclusion criteria for those who do not participate are recorded. Patients who agree to participate are invited to attend the practice for a baseline data collection consultation.

Once sixteen practices have been recruited and the relevant patient baseline data collected, at each centre an individual independent of the research team using computer-generated random numbers will allocate, with prior stratification, practices to intervention or control groups. Stratification will be according to the WTE for practitioners (less-than-two and two-or-more). Patient identification and baseline data collection occur prior to practice randomisation to minimize potential bias introduced by researchers and practitioners being aware of their allocation to either the intervention or control group. For intervention practices, meetings will be arranged to develop tailored practice care plans, deliver appropriate training, and support practitioners in reviewing patients four monthly for two years. Control practices will be visited again after one year and after two years, at which time points follow-up data will be collected.

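### Follow-up is timed from baseline, but allocation and training come later, so early practices fall short of 24 months of intervention and a two-year readmission count takes in pre-randomisation admissions

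*Protocol article*

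**What the plan says.** Four parts of the protocol article bear on the clock.

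- **Follow-up.** The Control Practices section gives the only explicit start point: "In control practices, data are collected at baseline, one and two years post baseline". It is written for control practices, but the sentence before it covers both arms: "Data are collected for patients in intervention and control practices in identical ways".
- **Allocation.** The Patient identification section places it late: "Once sixteen practices have been recruited and the relevant patient baseline data collected, at each centre an individual independent of the research team" allocates the practices. The order is deliberate: "Patient identification and baseline data collection occur prior to practice randomisation to minimize potential bias". The same section says "Control practices will be visited again after one year and after two years, at which time points follow-up data will be collected", without naming the point from which the years run.
- **Start of intervention.** Practice meetings and training follow allocation. The Initial target setting consultations section says the first patient consultation "takes place as soon as possible after baseline data collection, once training of practice staff has been completed".
- **Length.** The Background states "The intervention will be implemented over a 24 month period, with data collection at baseline, 12 months and 24 months". The Patient identification section has the team "support practitioners in reviewing patients four monthly for two years".

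Hospital readmission is a primary outcome (Data Analysis) and is powered on a two-year admission rate (Hospital re-admissions). Service use is collected in the questionnaire and the chart search over the preceding 12 months (Data Collection). Arms are compared at study completion, not as change from baseline (Randomised controlled trial analysis).

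**The concern.** The order is baseline, then a wait until the centre's sixteenth practice is ready, then allocation, then training, then the first consultation. Final measurement two years after baseline is fixed to the first of these steps, while the 24-month programme begins at the last. With any positive gap the programme cannot have run its stated length when the final data are taken. The wait for allocation is longest for the first practices in a centre and shortest for the last, so the shortfall is also uneven.

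Readmissions are the outcome most exposed. To obtain a two-year rate from 12-month look-backs, the year-1 and year-2 windows have to be joined. The year-1 window then contains time before anyone was allocated. Because the analysis compares arms at completion, admissions in that time would count as outcome events in both arms, and the difference between arms would shrink.

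**Working it through.** **Timeline.** Let G be the months from a practice's baseline to randomisation and T the months from randomisation to the first consultation. The protocol gives neither.

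- Exposure at 24 months after baseline = 24 − G − T. A 24-month programme would end at month 24 + G + T.
- Taking T = 0, exposure is 21, 18 or 15 months for G = 3, 6 or 9. The four-monthly reviews completed by month 24 number 5, 4 or 3, against 6 with no gap.
- Pre-randomisation share of the year-1 look-back = G/12: 25%, 50% or 75%.
- Pre-randomisation share of the year-2 look-back = 0 for G up to 12 months.

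**Readmission inputs.** The Hospital re-admissions section gives 43% over two years, a 20% reduction in control and a 50% reduction in intervention, and ICC 0.006.

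- Control: 0.43 × 0.80 = 34.4%. Intervention: 0.43 × 0.50 = 21.5%.
- As a check on the plan's own figure, the pooled two-proportion formula gives a total of 378 before clustering (408 with continuity correction), against the stated 356. The difference does not bear on this point.

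**Dilution model (assumptions: constant hazard, full effect from the start of intervention, T = 0, admissions counted over the two years from baseline).**

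- Two-year cumulative hazards: H_c = −ln(1 − 0.344) = 0.4216; H_i = −ln(1 − 0.215) = 0.2421.
- Intervention-arm rate with gap G: p(G) = 1 − exp{−[H_c × G/24 + H_i × (1 − G/24)]}. This gives 23.2%, 24.9% and 26.6% at G = 3, 6 and 9.
- If G is spread evenly across practices from 0 to a maximum of 3, 6 or 9 months, the average of p(G) is 22.4%, 23.2% or 24.1%.

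**Sample.** Two bases:

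- 48 × 20 × 0.875 × 0.70 = 588 completers (42 practices, 14 each). Effective N = 588/(1 + 13 × 0.006) = 545.
- The stated final sample of 635 (15 each). Effective N = 635/(1 + 14 × 0.006) = 586.

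**Power**, with n = effective N/2 per arm and two-sided 5%: Φ{[Δ√n − 1.96√(2p̄(1 − p̄))] / √(p₁(1 − p₁) + p₂(1 − p₂))}. With no gap and 588 completers: Δ = 0.129, n = 272.7, p̄ = 0.2795, so Φ{(2.130 − 1.244)/0.628} = Φ(1.41) = 92.1%.

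| Maximum gap, spread evenly from 0 | Intervention-arm rate | Power, 588 completers | Power, 635 completers |
|---|---|---|---|
| 0 | 21.5% | 92% | 94% |
| 3 months | 22.4% | 88% | 90% |
| 6 months | 23.2% | 82% | 85% |
| 9 months | 24.1% | 76% | 78.5% |

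Training time would add to every gap and lower these figures further.

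**The case against.** The strongest defence is that the sentence about revisiting control practices after one and two years follows directly on the allocation text and can be read as timed from allocation, and that an article may leave the exact visit anchor to the full protocol. That would carry weight if the article were silent. It is not: the Control Practices section names baseline as the start, so the two sections need reconciling on any reading.

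Other points limit the size of the matter, and they stand.

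- **Bias between arms.** A reader might infer that control and intervention practices are measured at different times and that the comparison is confounded with calendar time. The documents do not support this. Data are collected identically, and the wait for allocation falls on both arms. Nor does the protocol assert that routine care is changing; its qualitative work only explores the effect of any policy changes.
- **Every outcome diluted.** Blood pressure, cholesterol and SF-12 are measured at a point in time and have no window to contaminate. They lose only exposure time, and nothing in the documents shows how much their effect depends on the last few months of it.
- **All readmission data affected.** The year-2 look-back is clean if the gap is 12 months or less. The dilution arises in the year-1 look-back and in a two-year count that joins both.
- **A larger power loss.** Giving every practice the same gap of 3, 6 or 9 months would put power at 82%, 68% or 51% with 588 completers. That contradicts the mechanism, since the last practices in a centre wait hardly at all for allocation.

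**Conclusion.** The point holds as an inconsistency in the time origin with a dilution effect. For any positive gap, follow-up two years after baseline, allocation after the centre's last baseline, consultations after training, and 24 months of intervention by the final measurement cannot all be true. Practices recruited early in a centre lose most exposure, and a joined two-year readmission count includes pre-randomisation admissions.

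The size depends on a gap the protocol neither states nor limits. Under the even-spread assumption, a maximum wait of 3 months costs about 4 percentage points of readmission power. A maximum wait of 9 months takes it to 76% with 588 completers or 78.5% with 635, just under the planned 80%. These figures rest on constant hazard, immediate full effect, a count over the two years from baseline and no training time. Readmissions are the outcome chiefly affected. This should be corrected, but it does not threaten the validity of the randomised comparison.

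**What to change.** Keep baseline before allocation, since that order protects against selection bias. Then:

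1. Time the 12- and 24-month follow-up in both arms from the centre's randomisation date, with the same window in each arm.
2. Have the two-year chart search count readmissions from randomisation to 24 months.
3. Report, by practice and arm, the interval from baseline to randomisation and, for intervention practices, from randomisation to first consultation.
4. Reconcile the Background, Patient identification, Initial target setting consultations and Control Practices sections on when the clock starts.

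The cost is wording, rescheduling and a chart search over a longer span of records already being read. There are three downsides. The earliest practices are followed for longer in calendar time. Follow-up of sixteen practices, about 320 patients (16 × 20), bunches around one date in each centre and adds to the research nurses' load. A short training period remains inside the window, so exposure should be described as 24 months from randomisation, not as 24 months of delivered intervention.
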